## Patient registration

1. The principal investigator or co-investigator will obtain written consent from the patient, determine eligibility via any tests or interviews required to confirm eligibility, and then register and allocate the patient.
2. The eligibility and allocation test items will be entered into the EDC, and registration and allocation will be performed based on the eligibility assessment results. Registered study participants (including those determined to be “ineligible” by the EDC) will be assigned a patient identification number, and the group to which the eligible cases will be assigned will be displayed.
3. The medical institution conducting the study will create an “anonymization correspondence table” and enter numbers in it to prevent patient mix-ups. The principal investigator, co-investigator, or research collaborator will maintain the original data at the medical institution.

### Eligibility determination, registration, and allocation testing items

Upon eligibility determination, the following will be recorded and entered into the EDC:

・eGFR*, UACR* levels

・HbA1c, serum potassium levels

・LVEF* values

Then, at the time of registration and allocation, the following will be recorded and entered into the EDC:

・Date of consent, age at the time of consent, date of birth, and sex

・Use of SGLT2 inhibitors, eGFR* level

*Data obtained after obtaining consent will be prioritized; however, in the absence of this information, data from within 3 months prior to consent can be used

### Patient background

Duration of diabetes, presence or absence of complications/history of hypertension, dyslipidemia, ischemic heart disease, stroke, lower limb arteriosclerosis obliterans, or heart failure, primary underlying chronic renal failure disease including diabetic and non-diabetic nephropathy (chronic glomerulonephritis, nephrosclerosis, polycystic kidney disease, collagen disease-related nephropathy, or others)

## Scheduled observation and testing items

1. Baseline (Day 0)

In principle, a baseline test will be conducted within 60 days of obtaining consent, and administration of the study drug will begin the next day. If eligibility determination and baseline are conducted on the same day, the same data can be used for overlapping items.

1. Physical examination findings:

Height*, weight, clinic blood pressure (systolic and diastolic), clinic pulse rate

Optional: Home blood pressure (systolic and diastolic), home pulse rate

1. CAVI:

The device that measures CAVI (Basera) is approved as a medical device (blood pressure pulse wave inspection device) and is used to measure non-invasive blood pressure, electrocardiogram, phonocardiogram, and pulse wave chart to test arterial distensibility or blood flow disorder in the blood vessels of the lower limbs. Measurements are performed with reference to Appendix 2 (Basera Test Guide).

1. UACR** levels
2. Serum creatinine, eGFR, serum cystatin C** levels
3. Other biomarkers: (Outsourced measurement)

Blood (Pentosidine)

Urine (type IV collagen, α1-MG, β2-MG, NGAL, NAG, and L-FABP creatinine ratio).

1. Proteomics (outsourced measurement)
2. Blood tests:

Hemoglobin, hematocrit, serum albumin and potassium levels, HbA1c***, plasma aldosterone concentration, plasma renin activity

1. Cardiac ultrasound examination (optional)****:

LVEF, septal e′, lateral e′, mitral orifice blood flow velocity waveform (E), E/e′, LVMI, LAVI

1. Concomitant medications:

ACE inhibitors, ARBs, ARNIs, β-blockers, calcium antagonists, diuretics, statins, insulin, metformin, SGLT2 inhibitors, GLP-1 receptor agonists, DPP-4 inhibitors, iron preparations, ESAs, HIF-PH inhibitors, and hyperkalemia medications

During the observation period, in principle, no new administration of SGLT2 inhibitors and no changes in the dosage and administration of concomitant medications will be implemented.

* Data obtained after obtaining consent will be prioritized; however, in the absence of this information, data from within 3 months prior to consent can be used.

**Baseline data will be prioritized; however, if the baseline data is unavailable, data within 3 months from the baseline may be used.

*** Baseline data will be prioritized; however, if the baseline data is unavailable, data from the time of eligibility determination may be used.

**** Baseline data will be prioritized; however, if the baseline data is unavailable, data from 3 months prior to obtaining consent up to baseline may be used.

1. Week 4 (Day 28, allowable range for observation and testing: Days 21–35)
2. Physical examination findings:

Weight, clinic blood pressure (systolic and diastolic), clinic pulse rate

Optional: Home blood pressure (systolic and diastolic), home pulse rate

1. Serum creatinine levels and eGFR
2. Blood test: serum potassium levels
3. Week 12 (Day 84, allowable range for observation and testing: Days 70–98)
4. Physical examination findings:

Weight, clinic blood pressure (systolic and diastolic), clinic pulse rate

Optional: Home blood pressure (systolic and diastolic), home pulse rate

1. UACR levels
2. Serum creatinine, eGFR, serum cystatin C levels
3. Blood tests: serum potassium and HbA1c levels
4. Week 24 (Day 186, allowable range for observation and testing: Days 154–182)
5. Physical examination findings:

Weight, clinic blood pressure (systolic and diastolic), clinic pulse rate

Optional: Home blood pressure (systolic and diastolic), home pulse rate

1. CAVI:
2. The device that measures CAVI (Basera) is approved as a medical device (blood pressure pulse wave inspection device) and is used to measure non-invasive blood pressure, electrocardiogram, phonocardiogram, and pulse wave chart to test arterial distensibility or blood flow disorder in the blood vessels of the lower limbs. Measurements are performed using Appendix 2 (Basera Test Guide) as a reference.
3. UACR levels
4. Serum creatinine, eGFR, serum cystatin C levels
5. Other biomarkers: (Outsourced measurement)

Blood (Pentosidine)

Urine (type IV collagen, α1-MG, β2-MG, NGAL, NAG, and L-FABP creatinine ratio).

1. Proteomics (outsourced measurement)
2. Blood tests:

Serum potassium and HbA1c levels, plasma aldosterone concentration, plasma renin activity

1. Cardiac ultrasound examination (optional):

LVEF, septal e′, lateral e′, mitral orifice blood flow velocity waveform (E), E/e′, LVMI, LAVI

1. Concomitant medications:

ACE inhibitors, ARBs, β-blockers, calcium antagonists, diuretics, statins, insulin, metformin, SGLT2 inhibitors, GLP-1 receptor agonists, DPP-4 inhibitors, iron preparations, ESAs, HIF-PH inhibitors, and hyperkalemia medications

## *The method for measuring blood pressure at home should be based on the blood pressure handbook provided by the Japanese Society of Hypertension, and in principle, morning measurement results should be collected.

## Observation and testing items as-needed

1. Compliance with the study drug

Date of initiating administration, dosage (mg/day), reason for discontinuing administration, end date of administration, date of change in dosage (increase or decrease), changed dosage, reason, remaining quantity of medication

1. Adverse events (from consent to week 24):

Name of the adverse event, date of onset, severity, seriousness (serious/non-serious), presence or absence of causal relationship with the study (if “yes,” name of drug or test item suspected to be related), causal relationship with the study drug, predictability (known/unknown), outcome (recovered, improved, not recovered, with sequelae, death, unknown), and date of outcome

## Central testing

SRL, Inc. will centrally measure blood biomarkers (pentosidine) and urinary biomarkers (type IV collagen, α1-MG, β2-MG, NGAL, NAG, L-FABP creatinine ratio). SRL, Inc. will also collect and measure anonymized blood and urinary biomarker samples. Moreover, SRL, Inc. will collect and freeze samples for proteomics analysis, which will then be transported to a testing institution designated by the Department of Cardiology at Saga University Hospital while still anonymized.

Procedures for collecting, transporting, and measuring samples, as well as providing test results, will follow the standard operating procedures separately established by SRL, Inc. and the testing institutions designated by the Department of Cardiology at Saga University Hospital.

## Overview of the study drug

This study will use the test drugs provided by Bayer Yakuhin, Ltd listed below. For details, please refer to the latest package insert.

### Active drug

Generic name: Finerenone

Brand name: Kerendia tablets 10 mg/20 mg

Manufactured and sold by: Bayer Yakuhin Co., Ltd.

### Placebo

Tablets that look identical to the real medicine but contain no active ingredients

Ingredients: Tablet (lactose hydrate, microcrystalline cellulose, and magnesium stearate), film coating (hypromellose, talc, titanium oxide, yellow ferric oxide, and red ferric oxide)

### Efficacy and effectiveness

CKD with type 2 diabetes

However, this does not include patients with end-stage renal disease or those undergoing dialysis.

Caution (efficacy and effects)

1. This drug should be administered to patients receiving ACE inhibitors or ARBs, except when these treatments are not appropriate.
2. Because the administration of this drug may decrease eGFR, the appropriateness of administering this drug to patients with eGFR < 25 mL/min/1.73 m^2^ should be carefully considered after considering the risks and benefits.
3. In the Japanese subpopulation, the hazard ratio of this drug versus placebo for the renal composite endpoint, the primary endpoint of the global phase III study (Study 16244), was 0.911, while the hazard ratio of this drug versus placebo for renal failure, a component of the primary endpoint of the global phase III study (Study 16244), and for the renal composite endpoint, a secondary endpoint of the global phase III study (Study 17530) was > 1. The drug’s effect in preventing progression to renal failure may be weaker in Japanese patients as compared to that in the overall study population.
4. Select appropriate patients after thoroughly understanding the clinical results and the background of the patients enrolled in the clinical trial (primary disease, concomitant medications, renal function, and albuminuria).

### Dosage and administration

The usual dose of finerenone for adults is administered orally once daily at the following dosage:

eGFR, ≥ 60 mL/min/1.73 m^2^: 20 mg

eGFR < 60 mL/min/1.73 m^2^: Start administration at 10 mg and increase to 20 mg approximately 4 weeks after the administration initiation, depending on serum potassium levels and eGFR.

Caution (dosage and administration)

1. Serum potassium levels and eGFR should be measured 4 weeks after initiation of administration, resumption, or dose increase, and periodically thereafter; the dosage should be adjusted according to the table.

| Serum potassium level (mEq/L) | Dose adjustment |
| --- | --- |
| ≤ 4.8 | If the dose is 20 mg once daily, maintain dose;  If the dose is 10 mg once daily, increase dose to 20 mg once daily (only if eGFR has not decreased by > 30% since the previous measurement). |
| 4.8–5.5 | Maintain dose |
| > 5.5 | Discontinue |

After discontinuing administration, if serum potassium levels drop below 5.0 mEq/L, administration may be resumed at 10 mg once daily.

1. Bioequivalence of the 10 mg and 20 mg tablets has not been demonstrated; therefore, 10 mg tablets should not be used for the 20 mg dose.

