## Method of study drug administration

### Method of study drug administration

Study participants will be instructed to orally self-administer finerenone or placebo once daily (preferably at approximately the same time in the morning every day). The study participants with a baseline eGFR < 60 mL/min/1.73 m^2^ will be administered a starting dose of 10 mg/day of finerenone (placebo group, the equivalent of 10 mg/day), the dose will be increased to 20 mg/day (placebo group, the equivalent of 20 mg/day) in principle 4 weeks after the first administration in accordance with the manufacturer’s latest instructions provided in the package insert. Moreover, study participants with a baseline eGFR ≥ 60 mL/min/1.73 m^2^ will be administered a starting dose of 20 mg/day of finerenone (placebo group, the equivalent of 20 mg/day). After starting or increasing the study drug dose, it will be reduced or suspended depending on the participants medical condition including changes in serum potassium levels and eGFR, referring to the manufacturer’s latest instructions provided in the package insert and the table below, and the details will be recorded in the case report forms (CRFs).

| Serum potassium level (mEq/L) | Dose adjustment |
| --- | --- |
| ≤ 4.8 | If the dose is 20 mg once daily, maintain dose  If the dose is 10 mg once daily, increase the dose to 20 mg once daily (only if eGFR has not decreased by > 30% since the previous measurement). |
| 4.8–5.5 | Maintain dose |
| > 5.5 | Discontinue |

Quoted from the 3rd edition of the package insert

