### Usage precautions

- 1. Contraindications (do not administer to the following patients):

1. Patients with a history of hypersensitivity to any of the ingredients in this drug.
2. Patients receiving itraconazole, ritonavir-containing preparations, atazanavir, darunavir, fosamprenavir, cobicistat-containing preparations, or clarithromycin
3. Patients with serum potassium level > 5.5 mEq/L at the start of the drug administration as their hyperkalemia may worsen
4. Patients with severe liver dysfunction (Child-Pugh class C)
5. Patients with Addison’s disease as the drug may worsen the patient’s condition
6. Important basic notes
7. Because hyperkalemia may occur, in principle, administration should be initiated in patients with serum potassium levels ≤ 4.8 mEq/L, and the serum potassium levels and eGFR should be measured 4 weeks after initiating, resuming, or increasing administration, and then periodically thereafter. Moreover, in patients with serum potassium level > 4.8 mEq/L at the start of administration, additional serum potassium measurements should be considered prior to the start of administration 4 weeks later, depending on the serum potassium level and the patient’s condition.
8. Because eGFR may decrease early during the administration of this drug, it should be administered with caution to avoid deterioration of renal function.
9. Dizziness due to the hypotensive effect of this drug may occur. Therefore, caution should be exercised by patients when working at heights, driving a car, or operating dangerous machinery.

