## **Safety endpoints**

The following analyses will be performed with the SS. Reported adverse events will be assigned a low-level term (LLT) code using the Medical Dictionary for Regulatory Affairs, Japanese (MedDRA/J). The version of MedDRA/J used for the analysis will be the latest version at the time of database fixation.

1. Serum potassium levels (blood test parameter)
2. Descriptive statistics calculations will be conducted, and histograms will be plotted for serum potassium levels and its participant-level change by treatment group and study visit. Inferential statistics calculations will be conducted for the population-level mean and its change by treatment group and study visit. If the distribution of values deviates significantly from normal distribution, the proportional change will be described with the geometric mean and its proportional change as appropriate.
3. For serum potassium levels at each time point, analysis will be performed using MMRM with the baseline values as covariates, allocation, study visit and their interactions as fixed effects, and the patient as a random effect. The REML method will be used for the analysis with compound symmetry structure set as the covariance structure. The Kenward–Roger method will be used to calculate the degrees of freedom. To assess the treatment effect at each time point, the between-group difference in the change in the mean value using the least squares mean will be estimated using the placebo group as the reference. At each time point, the output will be the *P* value for testing the null hypothesis that the between-group ratio is 0.
4. The frequency of serum potassium levels exceeding 5.5 and 6.0 mEq/L, and falling below 3.5 mEq/L will be calculated for baseline, 4, 12, and 24 weeks after the protocol treatment initiation.
5. At 4, 12, or 24 weeks after the protocol treatment initiation, frequency of events with serum potassium exceeding 5.5 and 6.0 mEq/L, or falling below 3.5 mEq/L will be tabulated. The denominator for the tabulation will be the number of SS cases with serum potassium data after the protocol treatment initiation.
6. Hyperkalemia (adverse event)

The frequency of hyperkalemia reported as an adverse event will be tabulated. The denominator for the tabulation will be the SS.

1. Adverse events and side effects

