**Supplementary Table S4. Safety endpoints***

| **Event** | **Finerenone**  **(*n* = 51)** | **Placebo**  **(*n* = 50)** |
| --- | --- | --- |
| Any adverse event | 8 (15.7) | 8 (16.0) |
| Any serious adverse event | 5 (9.8) | 5 (10.0) |
| Atrial fibrillation | 0 | 1 (2.0) |
| Cardiac failure | 0 | 1 (2.0) |
| Cataract traumatic | 0 | 1 (2.0) |
| Cholangitis acute | 1 (2.0) | 0 |
| COVID-19 | 1 (2.0) | 0 |
| Gastric cancer | 0 | 1 (2.0) |
| Interstitial lung disease | 1 (2.0) | 0 |
| Large intestinal polypectomy | 0 | 1 (2.0) |
| Pyelonephritis | 1 (2.0) | 0 |
| Thermal burn | 1 (2.0) | 0 |
| Documented serum potassium level† |  |  |
| >5.5 mEq/L | 0 | 0 |
| <3.5 mEq/L | 0 | 3 (6.0) |
| Investigator-reported hyperkalaemia | 1 (2.0) | 0 |
| Adverse event related to study drugs ‡ | 2 (3.9) | 1 (2.0) |
| Serious adverse event related to study drugs ‡ | 1 (2.0)§ | 0 |
| Adverse event leading to discontinuation of study drugs | 2 (3.9)¶ | 1 (2.0)‖ |

* Shown are adverse events (n [%]) that occurred after the initiation of the study drug. Serious adverse events were classified according to the preferred terms from the Medical Dictionary for Regulatory Activities.

† Data are counted based on laboratory results from weeks 4, 12, or 24.

‡ A causal relationship between any adverse event and study drug administration was based on the opinion of the reporting investigators.

§ Interstitial lung disease (interstitial pneumonia)

¶ Serious adverse events (interstitial lung disease and pyelonephritis)

‖ Non-serious adverse event (abnormal hepatic function)

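### No potassium or eGFR test is scheduled 4 weeks after the week-4 dose increase, and the SAP's potassium threshold counts leave out off-schedule values

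*Combined protocol and SAP*

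**What the plan says.** **Testing rule.** The protocol's drug overview, under Dosage and administration, reproduces the package insert: "Serum potassium levels and eGFR should be measured 4 weeks after initiation of administration, resumption, or dose increase, and periodically thereafter". Usage precautions repeats it: "the serum potassium levels and eGFR should be measured 4 weeks after initiating, resuming, or increasing administration, and then periodically thereafter".

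**Dose increase.** Method of study drug administration (2.4.1) says that for participants with baseline eGFR below 60 "the dose will be increased to 20 mg/day (placebo group, the equivalent of 20 mg/day) in principle 4 weeks after the first administration". It ties this step to the latest package insert, and it makes later reduction or suspension depend on, among other things, changes in potassium and eGFR.

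**Schedule.** Table 1 and the visit list in section 4.3 place potassium and creatinine/eGFR at baseline and weeks 4, 12 and 24. The two visits that matter here are "Week 4 (Day 28, allowable range for observation and testing: Days 21–35") and "Week 12 (Day 84, allowable range for observation and testing: Days 70–98"). The as-needed items cover drug compliance and adverse events, with no unscheduled potassium or eGFR. None of the listed amendments adds a test between weeks 4 and 12.

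**Analysis.** SAP, Safety endpoints, counts threshold crossings at baseline and weeks 4, 12 and 24. Then, for weeks 4, 12 or 24 taken together, "frequency of events with serum potassium exceeding 5.5 and 6.0 mEq/L, or falling below 3.5 mEq/L will be tabulated". The footnote to Supplementary Table S4 confirms the counting: "Data are counted based on laboratory results from weeks 4, 12, or 24". Hyperkalemia reported as an adverse event is a separate tabulation on the safety set.

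**Dose table.** One row covers 4.8 mEq/L and below, and the next covers 4.8 to 5.5. Both rows include exactly 4.8.

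**The concern.** Section 2.4.1 brings the insert into the dosing procedure, and the insert text asks for a laboratory check 4 weeks after an increase. The study schedule makes no provision for that check. A site that follows the insert produces a potassium value with no named place in Table 1, the as-needed list or the SAP threshold counts. A site that follows only Table 1 has no value for that interval.

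Hyperkalemia is the one event named in the safety endpoint. A patient whose potassium is high between visits, and whose dose is then held, can be back below the threshold at the next scheduled visit. The laboratory count would not show that episode. The same gap can arise after a resumption, which the insert text also covers.

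**Working it through.** **Inputs.** Test interval: 4 weeks, i.e. 28 days (Dosage and administration; Usage precautions). Week-4 visit: Day 28, window 21–35. Week-12 visit: Day 84, window 70–98 (Table 1; section 4.3). Doses of on-treatment patients at week 24: Supplementary Table S1.

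**1. The plan's own visit days.** 7 × 4 = 28, 7 × 12 = 84 and 7 × 24 = 168, which agree with Table 1. The week-4 visit meets the rule for the first 4 weeks after starting. The problem concerns what follows an increase or a resumption.

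**2. When the rule asks for a test after a week-4 increase.** 28 + 28 = Day 56. Across the window: 21 + 28 = Day 49 to 35 + 28 = Day 63.

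**3. When the next scheduled test falls.**
- Nominal gap: 84 − 28 = 56 days (8 weeks).
- Shortest: 70 − 35 = 35 days (5 weeks).
- Longest: 98 − 21 = 77 days (11 weeks).

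The shortest gap exceeds 28 days, so no pair of in-window visits meets the rule. This assumes that the increase is made at the week-4 visit, as the protocol intends in principle. An increase made between Day 42 (70 − 28) and Day 70 (98 − 28) could have an in-window week-12 visit exactly 28 days later.

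**4. How many patients are concerned.** The number who moved from 10 to 20 mg is at least (started on 10) − (on 10 at week 24).

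| Arm | Started on 10 mg | On 10 mg at week 24 | Minimum increased | Share of 10 mg starters |
| --- | --- | --- | --- | --- |
| Finerenone | 26 | 8 | 18 | 18/26 = 69% |
| Placebo | 25 | 4 | 21 | 21/25 = 84% |
| Both | 51 | 12 | 39 | 39/51 = 76% |

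The 20 mg rows agree: 39 − 21 = 18, 43 − 22 = 21 and 82 − 43 = 39. These are net minimums. A patient who went up and came back down is not counted, nor is one who was off treatment at week 24. Table S1 gives no dates of increase.

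**5. What the threshold counts can see.** The count over weeks 4, 12 or 24 uses scheduled visits only, while its denominator is every safety-set patient with any potassium value after treatment start. Adding measurement occasions can raise an ever-crossed count or leave it unchanged; it cannot lower it. Table S4 shows 0 of 51 finerenone patients above 5.5 mEq/L, so on that denominator one patient with an off-schedule crossing would make it 1/51 = 2.0%.

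**6. The two rows at 4.8.** For a patient on 20 mg, both rows say maintain. For a patient on 10 mg at exactly 4.8, the first row says increase (subject to the eGFR condition) and the second says maintain.

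**The case against.** **The insert text is guidance, and no passage forbids an extra test.** This stands in part. The rule is worded as a recommendation in a drug overview, and the trial runs within regular insured care. The conflict is therefore an omission: schedule, as-needed list and SAP make no provision for a test that the protocol elsewhere asks for. A reader might infer that the protocol bars the test or that sites did not do it. The documents show neither.

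**Off-schedule episodes are not lost.** This also stands in part. A reader might infer that high potassium between visits has no place in the analysis, which is not so. The protocol's adverse event definition includes laboratory abnormalities, all adverse events up to the end of observation are collected, and the SAP tabulates reported hyperkalemia without tying it to a visit. Dose changes are recorded with date and reason. The SAP also has a rule for data at discontinuation in the safety analysis, though it does not plainly add those values to the week 4, 12 or 24 count.

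**Equal scheduled sampling in both arms is a defensible choice.** Agreed. A count over all samples depends partly on who was tested more often, which is why the scheduled-visit count should stay. Downward bias is possible but not shown.

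**Two stronger readings are not supported.** Table S4 has one investigator-reported hyperkalemia on finerenone beside zero values above 5.5. A reader might take that as a missed value, but no 5.5 cut-off defines the adverse event, so it may have been at or below 5.5. A reader might also call weeks 4 to 12 the period of highest risk. No passage says so. In Table S2 the mean potassium difference between arms is 0.3 mEq/L at week 4 and 0.2 at weeks 12 and 24; these means neither show nor exclude individual peaks.

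**Conclusion.** The point holds as an internal conflict that should be fixed. After a week-4 increase, the next scheduled potassium and eGFR test comes 56 days later (35 to 77), against the 4 weeks in the insert text that the dosing section invokes. An increase was common: at least 18 of 26 finerenone patients who started on 10 mg and were on treatment at week 24. The share increased exactly at week 4 is unknown.

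The SAP's laboratory threshold counts omit off-schedule values, so the ever-crossed count can be too low; by how much, if at all, cannot be told from the documents. The adverse event tabulation is a partial safeguard. The primary endpoint and its analysis are unaffected. The overlap at 4.8 mEq/L is a smaller, separate inconsistency that matters only for a patient on 10 mg. The EDC forms are not in the documents, so whether unscheduled potassium was recorded is not known.

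**What to change.** 1. Reconcile section 2.4.1, Table 1 with section 4.3, and the drug overview (Dosage and administration; Usage precautions) so that they agree on test timing after an increase or resumption. Reconcile the two dose-table rows at 4.8 mEq/L. No view is taken here on which clinical rule is right.
2. Record every potassium value after the first dose, including unscheduled and discontinuation samples, with its date.
3. Add a sentence to the SAP, Safety endpoints: the counts of patients ever above 5.5, ever above 6.0 and ever below 3.5 mEq/L use all post-dose values. Keep the by-visit tables, and report a scheduled-visit-only count alongside.
4. Since results are already tabulated, retrieve off-schedule values from source records and rerun the ever-crossed counts, or state in the report that they cover scheduled visits only.

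The cost is a protocol clarification, one data form, a short SAP change and some extra data entry. The drawback is that the all-values count depends partly on how often each patient was tested. Blinding limits that, and the scheduled-visit count beside it lets the reader judge it.
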